## **37. BROAD PROJECT AIMS**

4.1. To establish the immune response in the serum and bronchoalveolar lavage (BAL) as measured cross-sectionally and longitudinally during the three year post-LTx and the association with later episodes of acute rejection or the subsequent development of CLAD.

4.2. To determine whether episodes of viral, fungal or bacterial infection in the LTx recipient trigger further increases in the secretion of these biomarkers and thus act as an inflammatory stimulus.

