### **5.3 Acute Rejection**

Despite the use of maintenance immunosuppression, acute cellular rejection is a common problem post lung transplant with 34% of adult LTx recipients experiencing at least one episode during the first year

post-transplant. The lung allograft is particularly susceptible to alloreactivity with the incidence of acute rejection being higher following LTx compared to other solid organ transplants. Whilst the direct effects of acute rejection are usually controlled and reversed following high-dose intravenous steroid treatment, the indirect effects remain problematic, with episodes of acute rejection being strongly associated with the later development of chronic lung allograft dysfunction (CLAD). Given the need for invasive transbronchial biopsies to provide a histological diagnosis of acute cellular rejection, we have previously evaluated biomarkers in the blood and BAL and their association with acute rejection (2-5). Functional assays of T cell and B cell function in the blood may identify patients at higher risk of acute cellular rejection. Analysis of the BAL is very useful in providing mechanistic insights into the immunology of graft function and rejection following LTx. However, BAL findings seen in acute rejection must be interpreted in the context of those described in stable lung transplant recipients, and after taking into account the confounding nature of chronic airway infection.

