**Specific Aim #3: Determine the immunological profiles of the lower airways of lung transplant recipients**

We will characterise the immunological environment of the lower airways of LTx recipients at each timepoint (i.e. 2 weeks, 3, 6, 9, 12 and 18 months) by RNAseq of immune cells isolated from the lavage fluid. We will perform Mass Spectrometry of the lavage fluid to characterise the metabolome, lipidome and proteome. Bioinformatic integration of these datasets (see Aim 5) will allow us to gain deep insight into the immunological profiles of the patient groups.

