**At Bronchoscopies:**

- g) As part of routine post-transplant management lung transplant recipients attend for surveillance bronchoscopy at 1 day, 2 and 6 weeks and 3, 6, 9, 12 and 18 months post-transplant, at which point BAL samples are collected.
- h) On occasions of clinical concern, additional bronchoscopies may be scheduled as part of patient care. At these clinical relevant bronchoscopies, BAL samples are also collected.

30mls of BAL will also be collected from both the transplanted lung and the native lung of participants who receive a single lung transplant

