**42. INCLUSION/EXCLUSION CRITERIA**

Approximately 150 patients, including 10-15 single lung transplant recipients, will be enrolled at The Alfred Hospital

Inclusion Criteria

- Adults  $\geq 18$  years of age
- Lung Transplant Recipients
- Provide Written Consent

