### 43. ANALYSIS:

Descriptive statistics will be used to determine the baseline and clinical characteristics of the subjects in the study. Univariate analysis of the biomarkers and their association with the clinical end-points of acute rejection and CLAD will be performed using the Chi-square test for equal proportion, Student's t test for normally distributed continuous variables and the Mann-Whitney U test for non-normally distributed variables. Time to acute rejection and CLAD will be analyzed using univariate and multivariate Cox proportional hazards regression, adjusting for potential confounding factors and reported using the Kaplan Meier curves. All analysis will be performed using SAS version 9.2 (SAS Institute Inc., Cary, NC, USA). A two-sided p-value of 0.05 will be considered to be statistically significant.

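### The Cox and two-group analyses do not tie the biomarker sample to the event in time, so samples taken at or after rejection or CLAD can count as predictors

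*Supplement*

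**What the plan says.** All references are to version 4.0 in the Supplement.

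- **Question.** The Hypothesis (section 36) is that biomarkers predict rejection and the onset of CLAD. Aim 4.1 (section 37) concerns "the association with later episodes of acute rejection or the subsequent development of CLAD". The order is marker first, event afterwards.
- **Sampling.** Section 8.2.1 schedules BAL at day 1, weeks 2 and 6, and months 3, 6, 9, 12 and 18. It adds: "On occasions of clinical concern, additional bronchoscopies may be scheduled as part of patient care", and BAL is taken then too. Specific Aim #3 profiles the airway "at each timepoint (i.e. 2 weeks, 3, 6, 9, 12 and 18 months". Specific Aim #2 assesses *de novo* donor-specific antibody at 3 and 12 months.
- **Exception.** The eplet mismatch score (Specific Aim #1) is fixed at transplant.
- **Analysis.** Section 43 compares biomarkers by endpoint with chi-square, t and Mann-Whitney tests, and then states: "Time to acute rejection and CLAD will be analyzed using univariate and multivariate Cox proportional hazards regression", adjusted for possible confounders and reported with Kaplan-Meier curves. It adds: "A two-sided p-value of 0.05 will be considered to be statistically significant".
- **Follow-up.** Three years after transplant (section 8.3).

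Section 43 does not state the time origin, which of a patient's samples enters, whether covariates are fixed or time-updated, or what happens to samples taken at or after the event.

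**The concern.** The markers are collected over the same months in which rejection accrues. Two different errors are then possible, and nothing in section 43 excludes either.

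1. **Reverse order.** A sample taken after a rejection, or at the bronchoscopy that diagnoses it, may be raised by the event itself. Entered as a predictor, it makes a marker with no predictive value look harmful. Scheduled visits are exposed as well, because section 5.3 makes biopsy the basis for diagnosing rejection, and a surveillance visit may be the diagnosing one.
2. **Immortal time.** A patient must stay event-free to supply later pre-event samples. If those samples are reduced to an ever-high or peak value and treated as known at transplant, patients who last longer have more chances to score high. A useless marker then looks protective.

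The two-group tests have the same gap. At stake is whether a significant result can be read as prediction, which is the study's hypothesis, or only as association at or after diagnosis.

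**Working it through.** The documents contain no event count, effect size or power calculation, so there is no figure of the plan's own to reproduce.

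**Inputs from the documents.** N about 150 (section 42: "Approximately 150 patients, including 10-15 single lung transplant recipients, will be enrolled at The Alfred Hospital"); first-year acute rejection from section 5.3 ("34% of adult LTx recipients experiencing at least one episode during the first year"); the visit times above; 36 months of follow-up; two-sided 0.05.

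**Assumptions not in the documents.** Constant hazard for first rejection, carried beyond year 1; no deaths or dropout; the marker behaviour stated in each scenario.

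**Step 1: patients already rejected when the sample is taken.** At 12 months: 150 × 0.34 = 51, whatever the shape of the hazard within the year. For earlier visits, λ = −ln(1 − 0.34)/12 = 0.0346 per month and P(t) = 1 − exp(−λt).

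| Sample | P(rejected before) | Of 150 |
|---|---|---|
| 3 months | 9.9% | 15 |
| 6 months | 18.8% | 28 |
| 9 months | 26.8% | 40 |
| 12 months | 34.0% | 51 |

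With a front-loaded hazard (Weibull shape 0.8 to 0.6, still 34% at one year), the 3-month share rises to 12.8% to 16.5%.

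**Step 2: what the coding does to a marker with no predictive value.** Cox models were fitted to simulated cohorts of 150 followed for 36 months. The true hazard ratio is 1 throughout, and false positives should be 5%.

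| Coding | HR | p < 0.05 |
|---|---|---|
| 12-month marker, all patients, raised 0.25 SD by earlier rejection | 1.10 | 18% |
| Same, raised 0.5 SD | 1.21 | 49% |
| Same, raised 1.0 SD | 1.45 | 98% |
| Ever high before the event, fixed from transplant, 10% to 15% chance per visit, all eight visits | about 0.7 to 0.6 | about 45% to 70% |
| Peak of all pre-event samples, fixed from transplant | 0.57 per SD | 90% |
| Ever high, time-updated | 1.00 | 5.2% |
| 12-month marker, event-free patients, clock from month 12 | 0.99 | 6.0% |
| 12-month marker, event-free patients, clock from transplant | 0.99 | 6.0% |

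With only the six visits in Specific Aim #3, the ever-high coding gives 0.57 to 0.62, with 64% to 82% false positives.

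The 0.5 SD, peak and last three rows use 600 runs, where the standard error of a 5% rate is √(0.05 × 0.95/600) = 0.9 points. The 0.25 and 1.0 SD rows use 200 runs.

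**Step 3: reading the table.** The two errors pull in opposite directions, and both disappear under landmark or time-updated coding. The last two rows agree because no event falls before month 12 among patients who are event-free then. A Kaplan-Meier curve for that group drawn from transplant would still be flat to month 12, and so too favourable.

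**The case against.** - **The plan does not prescribe a biased analysis.** A reader might infer that immortal-time bias is built in. The text does not support that: Cox regression accepts time-updated covariates, and fixed, ever-high or peak coding appears nowhere. The aims describe markers visit by visit, and a single-visit marker in event-free patients is unbiased. This stands. The defect is that the choice is left open.
- **Not every summary misleads.** One might extend the argument to the mean of pre-event samples. For a marker without a time trend, that gave HR 0.98 to 1.02 with about 7% to 13% false positives: some inflation, but not the distortion seen with ever-high or peak coding.
- **Samples at diagnosis have a legitimate use.** The Summary (section 35) and aim 4.1 plan cross-sectional as well as longitudinal work, and section 8.2.1 describes collection, not analysis. It would go too far to say that these samples will be pooled with the rest. Section 43 does not say that they will be kept apart.
- **Excluding patients with an earlier rejection is not neutral.** Aim 4.1 speaks of episodes, and a sample taken after one episode may properly precede the next. This stands and shapes the fix.
- **Such detail often sits in a separate SAP.** None is shown, and section 43 is short. But it already fixes the tests, model, software and significance level, while the order of sample and event decides whether the stated hypothesis is being tested. This objection lowers the weight of the point without removing it.

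**Conclusion.** The point holds as a gap in the specified analysis. The aim requires the marker to come before the event, the sampling schedule does not ensure it, and section 43 does not impose it. About 51 of 150 patients could have rejected before a 12-month sample; that count rests only on the protocol's 34% and N, with every patient followed to month 12.

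The hazard ratios of about 1.1 to 1.45 and 0.6 to 0.7 are illustrations. They depend on the assumed marker behaviour, a constant hazard over 36 months, and no deaths or dropout. They show that the bias can be large and can run either way, not what this study will find.

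Three limits apply. The eplet score is unaffected. The calculations concern first rejection only, because the documents give no CLAD rate. And one should not conclude that the hypothesis cannot be tested with these data: dated serial samples and three years of follow-up are enough once the analysis respects time order.

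**What to change.** Amend section 43, separately for time to first rejection and time to CLAD:

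1. Use **landmark Cox models** at named surveillance visits (for example 3 and 12 months). Time zero is the sample date, and only patients free of that endpoint enter; a patient diagnosed at that same visit is not event-free. Alternatively, use a **start-stop Cox model** with the last marker value strictly before the event.
2. Draw Kaplan-Meier curves from the landmark.
3. Report samples from the diagnosing bronchoscopy separately, as cross-sectional or diagnostic analyses.
4. Restrict two-group tests offered as evidence of prediction to pre-event samples.
5. If repeat rejection episodes are of interest, use a recurrent-event start-stop model rather than dropping patients with an earlier episode.

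The cost is wording and programming; no new data are needed. Later landmarks lose patients: under the assumptions above, about 150 − 15 = 135 remain for first rejection at 3 months and 150 − 51 = 99 at 12 months, with correspondingly fewer events.

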## **35. SUMMARY**

Transplantation saves the lives of patients with end stage lung disease. Better operative techniques, anaesthesia, organ preservation and more potent immunosuppression have improved outcomes significantly but long-term graft survival remains unchanged. Transplanted lungs are lost due to an ill-defined process called chronic lung allograft dysfunction (CLAD) that is characterized by either fibrosis of the airways (bronchiolitis obliterans syndrome = BOS) or of the lung architecture (restrictive allograft syndrome = RAS) (1). CLAD is characterised by a drop in lung function, that once established is irreversible. The major risk factors for CLAD are i) acute rejection as diagnosed on lung biopsy and ii) infection, particularly CMV and aspergillus. To date, biomarkers have not been identified that can diagnose acute rejection or predict the early onset of CLAD.

We have previously explored a number of biomarkers and demonstrated an association with allograft dysfunction following lung transplant (LTx). We have shown that activin and follistatin levels vary with time from LTx and reflect a proinflammatory environment (2,3). We continue to explore the role of NK cells following LTx having previously shown that NK cells become activated in patients undergoing acute rejection or CMV infection (4, 5). Collaborative research with the Doherty Institute has demonstrated a link between immune cells that control CMV and the later development of CLAD (6). We now wish to extend this biomarker approach with a new prospective cohort of LTx patients who will provide blood and BAL samples to allow further interrogation of immune and infectious links to allograft dysfunction following LTx.

Identifying CLAD at an early stage, may allow therapeutic interventions to interrupt the progression to irreversible damage to the transplanted lung. We propose to analyse in both a cross-sectional and longitudinal study whether a series of biomarkers can predict for episodes of acute rejection or the development of CLAD in a cohort of patients undergoing LTx at the Alfred Hospital.

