**8.3 Participant Involvement:**

All participants will be followed for a total of 3 years following lung transplant.

Lung transplant recipients enrolled in the study would not need to make any additional trips to the Alfred hospital nor undertake any additional investigations. Collection of research related samples at bronchoscopies will coincide with routine biopsy, blood and BAL collections and will not require additional procedures for the participants.

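### Kaplan-Meier curves for time to CLAD take no account of death before CLAD and, if such deaths are censored, would overstate CLAD risk

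*Supplement*

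**What the plan says.** Section 43 (Analysis) of protocol version 4.0 sets out two kinds of analysis.

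- Time to event: "Time to acute rejection and CLAD will be analyzed using univariate and multivariate Cox proportional hazards regression". On covariates and presentation, the same sentence says that this is done "adjusting for potential confounding factors and reported using the Kaplan Meier curves".
- Univariate comparisons of biomarkers: "their association with the clinical end-points of acute rejection and CLAD will be performed using the Chi-square test for equal proportion", with the t test and the Mann-Whitney test for continuous markers.

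Section 8.3 gives the horizon: "All participants will be followed for a total of 3 years following lung transplant". Section 42 gives the size: "Approximately 150 patients, including 10-15 single lung transplant recipients, will be enrolled at The Alfred Hospital".

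Section 43 does not mention death, retransplantation, censoring, competing risks, cumulative incidence or a composite of CLAD and death, and no other part of version 4.0 supplies a rule. Survival appears in the study proposal (section 39) only as a long-term goal. The only event rate given is for acute rejection, in section 5.3: "34% of adult LTx recipients experiencing at least one episode during the first year". No separate analysis plan is shown.

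**The concern.** CLAD is a non-fatal endpoint, and a patient who dies without it can no longer develop it. The usual Kaplan-Meier analysis of such an endpoint censors that patient at death and in effect assumes that the later CLAD risk would have matched that of the survivors. The curve then describes a setting in which nobody dies first. Read as the share of recipients who develop CLAD by 3 years, it is too high whenever any such death occurs.

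What is at stake is mainly the comparison between marker groups. The hypothesis concerns markers of immune function and infection. It is plausible, though the documents do not say so, that some of these markers also relate to death. The overstatement would then be larger in the high-marker group, and the gap between the plotted curves would exaggerate the difference in actual CLAD risk.

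**Working it through.** **Inputs from the protocol.** Follow-up 3 years (section 8.3); about 150 patients (section 42); 34% acute rejection in year 1 (section 5.3). There is no CLAD rate, death rate, event count or power calculation, so there is no figure of the plan to reproduce. All CLAD and death rates below are assumptions.

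**Step 1: size of the overstatement for CLAD.** Let C be the true 3-year cumulative incidence of CLAD and D the proportion who die before CLAD within 3 years. With constant cause-specific hazards, CLAD takes the share C/(C+D) of the total hazard, and the event-free proportion at 3 years is 1-C-D. With deaths censored,

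1-KM = 1 - (1-C-D)^(C/(C+D)).

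For C = 0.30 and D = 0.10: 1 - 0.60^0.75 = 0.318.

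| True CLAD | Death before CLAD | 1-KM | Ratio |
|---|---|---|---|
| 20% | 10% | 21.2% | 1.06 |
| 20% | 25% | 23.3% | 1.17 |
| 30% | 10% | 31.8% | 1.06 |
| 30% | 15% | 32.9% | 1.10 |
| 30% | 20% | 34.0% | 1.13 |
| 30% | 25% | 35.3% | 1.18 |
| 40% | 10% | 42.6% | 1.06 |
| 40% | 25% | 47.6% | 1.19 |

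**Step 2: the same question from the other side.** Fix the value that Kaplan-Meier would show and a net 3-year death risk (the risk if CLAD did not occur). Put hc = -ln(1-net CLAD)/3 and hd = -ln(1-net death)/3. The actual incidence is CIF = hc/(hc+hd) x (1 - exp(-3(hc+hd))). For 1-KM of 20% to 50% and net death of 5% to 30%, the excess is 0.5 to 7.1 percentage points. Putting half of the cumulative death hazard in year 1 raises the upper end to 8.4 points.

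**Step 3: marker groups.** Take a two-group marker with a CLAD hazard ratio of 2, and a reference group with net CLAD 30% and net death 15%. Suppose the marker also triples the death hazard.

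- Reference group: 1-KM 30.0%, CIF 27.8%, excess 2.2 points.
- High-marker group: 1-KM = 1 - 0.7^2 = 51.0%, CIF 41.5%, excess 9.5 points.
- Gap between groups: 51.0 - 30.0 = 21.0 points on Kaplan-Meier, against 41.5 - 27.8 = 13.7 points in actual CLAD incidence.

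**Step 4: acute rejection.** Apply the same formula over 1 year, taking 34% as the Kaplan-Meier value. One-year net death of 5%, 10% or 15% gives an actual incidence of 33.2%, 32.4% or 31.6%. The excess is 0.8 to 2.4 points.

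**The case against.** Much of the case on the other side stands.

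- **The plan states no censoring rule.** A reader might infer that it instructs deaths to be censored. It does not; that follows only from ordinary use of the named method. Such rules are often left to a separate analysis plan. Even so, the protocol itself chooses Kaplan-Meier, and a cumulative incidence curve is a different and better-suited estimator, so this is more than missing detail.
- **The Cox model is sound.** With deaths censored it estimates a cause-specific hazard ratio, which suits the stated aim of association. Version 4.0 sets no objective to estimate absolute 3-year CLAD risk. The defect lies in the curves and in any risk read from them.
- **The size is modest.** At a true 30% with 10% or 15% death, the excess is 1.8 or 2.9 points. The sampling standard error of 30% in 150 patients is sqrt(0.3 x 0.7/150) = 3.7 points. But the overstatement is systematic: it does not shrink with more patients, and it can differ between marker groups.
- **The yes/no tests.** A reader might infer that counting early deaths as CLAD-free in the chi-square test is a coding error. It is not. With complete 3-year follow-up, CLAD cases divided by all patients is the cumulative incidence with death as a competing event, the very quantity recommended here. What remains is narrower: in the t and Mann-Whitney comparisons, a non-CLAD group that includes patients who died early is heterogeneous, and the plan does not say where those patients go.
- **Reversal.** A reader might also infer that the yes/no analysis would in general reverse a marker's association. Under the step 3 assumptions the 3-year risk ratio is 1.71, 1.49, 1.31 and 1.10 at death hazard ratios of 1, 3, 5 and 8. It falls just below 1 (0.99) only at 10, which means about 80% net death in the high-marker group. A ratio clearly below 1 (0.87) appears when the marker has no effect on the CLAD hazard and triples the death hazard. Reversal therefore needs a null or weak CLAD effect with a strong death effect.

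**Conclusion.** The point holds for the Kaplan-Meier curves for CLAD and should be mended. If deaths before CLAD are censored, the direction of the error is certain. Its size cannot be fixed from the documents: it is about 6% to 19% in relative terms for a true 3-year CLAD incidence of 20% to 40% and death before CLAD of 10% to 25%, under constant hazards. Unequal overstatement between marker groups rests on the further assumption that the marker relates to death. For acute rejection the effect is likely small. The documents do not support calling the Cox analysis invalid, calling early deaths wrongly coded in the chi-square test, or expecting reversed associations as a rule.

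**What to change.** In section 43:

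- Replace the Kaplan-Meier curves for CLAD with Aalen-Johansen cumulative incidence curves, with death before CLAD (and retransplantation, if any occurs) as competing events. Do the same for acute rejection, for consistency.
- Keep the Cox models, state that they are cause-specific with deaths censored, and report a companion cause-specific model for death without CLAD.
- Add CLAD-or-death as a sensitivity endpoint.
- Keep the 3-year chi-square comparison if wanted, with all patients in the denominator, and describe it as a comparison of cumulative incidence.
- For the t and Mann-Whitney comparisons, show patients who died without CLAD as a separate group, or rely on the time-to-event model. Do not restrict any of these to 3-year survivors, which would condition on survival.

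The cost is some wording and a little more analysis work. No extra patients, visits or samples are needed, provided that dates of death are recorded during the 3-year follow-up, which section 8.3 implies but does not state. The reported CLAD risk will be slightly lower.

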## **36. HYPOTHESIS**

The identification of biomarkers of immune function and infection in the blood and lung will predict episodes of acute rejection and the onset of chronic lung allograft dysfunction (CLAD) following LTx.

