**Specific Aim #4: Identification of the bacterial, fungal and viral communities in lung transplant recipients**

*Bacterial and fungal community identification:* Fungal and bacterial DNA will be amplified and sequenced. The virome will be characterised, using two experimental approaches in order to ensure we capture a complete and informative dataset. First, PCR amplification will be used to analyse the total set of BAL samples informing on the carriage of a specific set of RNA and DNA viruses, including a panel of anelloviruses which we hypothesize will be highly relevant in the lung transplant setting. In a second step, we will refine the patient pool for analysis based upon the clinical, immunological, bacterial, fungal and viral PCR results and perform metagenomic sequencing providing us with in-depth unbiased data on viral carriage.

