**Specific Aim #5: Bioinformatics and integration of microbial, immunological and clinical datasets**

Network-based approaches have emerged as a powerful way to study microbial systems and analyse high-dimensional datasets. Using the bacterial, fungal and viral sequencing datasets, we will construct and combine ecological networks using dissimilarity and correlation-based methods. This will firstly allow us to determine the extent to which bacterial, fungal and viral communities are connected by causal relationships, and in particular, we can identify “key-stone” species which would be predicted to play a major role in community dynamics and consequently the immunological and health status of the transplant recipient.

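### One unadjusted 0.05 threshold is the only significance rule for a two-endpoint biomarker search that now includes RNAseq, mass spectrometry and microbial sequencing

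*Supplement*

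**What the plan says.** All references are to protocol version 4.0.

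- **Endpoints and tests.** Section 43: "Univariate analysis of the biomarkers and their association with the clinical end-points of acute rejection and CLAD will be performed", using chi-square, t or Mann-Whitney tests. It continues: "Time to acute rejection and CLAD will be analyzed using univariate and multivariate Cox proportional hazards regression". Neither endpoint is named primary, and no primary biomarker is named.
- **Criterion.** Section 43 closes with: "A two-sided p-value of 0.05 will be considered to be statistically significant". The sentence is not limited to any subset of markers, and no adjustment is mentioned.
- **What is measured.** Section 40, Specific Aim #3, profiles the lower airways "at each timepoint (i.e. 2 weeks, 3, 6, 9, 12 and 18 months) by RNAseq of immune cells isolated from the lavage fluid" and adds: "We will perform Mass Spectrometry of the lavage fluid to characterise the metabolome, lipidome and proteome". Specific Aim #4 adds: "Fungal and bacterial DNA will be amplified and sequenced", plus characterisation of the virome.
- **Integration.** Specific Aim #5 says of the microbial datasets: "we will construct and combine ecological networks using dissimilarity and correlation-based methods". It states no error rate and no test against acute rejection or CLAD.
- **Claim to be supported.** Section 36 (Hypothesis) says that the biomarkers "will predict episodes of acute rejection and the onset of chronic lung allograft dysfunction (CLAD) following LTx".

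**The concern.** A per-test threshold of 0.05 suits one pre-chosen marker or a very short list. It gives no control over how many wrong markers are named when hundreds or thousands of features are screened. The protocol does not present the screen as hypothesis-generating. The hypothesis is about prediction, and section 39 (Study Proposal) expects the resulting biomarkers to inform how immunosuppression is used. If the rule is followed as written, a published list of significant markers could contain many null ones, with nothing in the plan to tell them apart.

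There is a second, related gap. The stated outputs are association p-values and Cox regression in the same patients who supply the candidate markers. Those outputs show association. They do not show that a marker predicts an outcome in patients not used to select it.

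**Working it through.** **Inputs from the documents.** Per-test alpha 0.05, two-sided, and two endpoints (section 43). Seven data layers: RNAseq, metabolome, lipidome and proteome (Aim #3), and bacterial, fungal and viral (Aim #4). The documents give no feature counts, no expected share of true associations, no power and no error rate across tests, so the plan has no figure of its own to reproduce. Everything below that depends on those quantities is an assumption shown over a range.

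**Step 1: the smallest plausible search.** Suppose each layer were reduced to one summary test per endpoint, giving 7 × 2 = 14 tests. If all are null and independent, the chance of at least one false positive is 1 − 0.95^14 = 51%. With 20 targeted markers and two endpoints (40 tests) it is 1 − 0.95^40 = 87%. Correlation between tests would change these probabilities.

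**Step 2: expected false positives in a feature-level screen.** The expected number is 0.05 × number of null tests. Correlation does not alter this expectation.

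- 1,000 null features, one endpoint, one set of tests: 0.05 × 1,000 = 50.
- The same features on both endpoints: 0.05 × 2,000 = 100.

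Repeating the screen at further timepoints would multiply these counts, but section 43 does not say that every feature is tested at every timepoint, so no multiplier is applied.

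**Step 3: what share of the declared markers would be false?** Let p be the share of tested features truly associated. As a ratio of expected counts,

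false share = 0.05(1 − p) / [0.05(1 − p) + p × power].

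For example, take 1,000 features with p = 5% and 80% power. There are 950 null features giving 47.5 false hits and 50 true ones giving 40 true hits, so the false share is 47.5 / 87.5 = 54%.

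| Assumed p | Power 80% | Power 50% | Power 30% |
|---|---|---|---|
| 1% | 86% | 91% | 94% |
| 5% | 54% | 66% | 76% |
| 10% | 36% | 47% | 60% |
| 20% | 20% | 29% | 40% |

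**Step 4: break-even.** Setting the false share to one half gives p = 0.05 / (0.05 + power):

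- 80% power: 0.05 / 0.85 = 5.9%
- 50% power: 0.05 / 0.55 = 9.1%
- 30% power: 0.05 / 0.35 = 14.3%

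Below these values most declared markers are false. Above them most are real.

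**The case against.** **Section 43 does not name the omics layers.** Its wording has been carried unchanged through the versions, and Aim #3 sends its datasets to Aim #5 for integration. The threshold may never have been meant for individual genes or metabolites. This has some force: applying section 43 feature by feature is a reading, not an explicit statement. But Aim #5 describes only networks of bacterial, fungal and viral data, with no error rate and no link to either endpoint. Section 43 therefore remains the only criterion in the protocol for relating any measured marker to rejection or CLAD.

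**Omics error control is often left to a separate analysis plan, and none is shown.** Its absence alone would not be a fault. The point here is the rule that the protocol does state, which sets a bare 0.05 without reserving the omics screens for another document.

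**The cohort is observational and exploratory, so strict family-wise control is debatable.** This stands, and it is why the fix uses a false discovery rate. The screens are not labelled exploratory, however, and the hypothesis claims prediction.

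**Stronger readings that the documents do not support.** A reader might infer that most declared biomarkers will be false. That depends on p and power, which are not given; at p = 20% with 80% power only one in five would be false. A reader might also multiply the counts by six timepoints for every platform. The six timepoints are attached explicitly only to RNAseq, and separate testing at each is not stated. Finally, a reader might treat 51 (34% of 150) as the number of rejection events available. The 34% in section 38 is a first-year background rate, whereas follow-up is three years.

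**Conclusion.** The concern holds in limited form. Version 4.0 states one unadjusted two-sided 0.05 threshold as its only significance rule for a two-endpoint search that includes several high-dimensional platforms. Applied as written to individual features, it would declare about 5% of null features significant for each endpoint and set of tests. Whether these would outnumber the real markers is conditional: they would if fewer than about 6% (80% power) to 9% (50% power) of features are truly associated.

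The conclusion assumes that section 43 is applied feature by feature. The feature counts, p and power used above are illustrative. Separately, the stated analyses can support claims of association but not, without internal validation, the predictive claim in the hypothesis.

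**What to change.** Replace the last sentence of section 43 with wording to this effect:

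1. For each endpoint, each omics or sequencing platform is controlled at a 5% Benjamini-Hochberg false discovery rate across all features and timepoints tested on that platform.
2. Unadjusted p-values below 0.05 are reported as descriptive only.
3. A marker is called predictive only after internal validation, for example a cross-validated C-index with all feature selection done inside the folds.

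A false discovery rate is preferable to Bonferroni here. As an illustration, take 51 patients with and 99 without first-year rejection (34% of 150) and a normal approximation: power ≈ Φ(d / √(1/51 + 1/99) − z). For a difference of d = 0.5 SD, unadjusted power is Φ(2.90 − 1.96) = 83%. Under Bonferroni over 2,000 tests (1,000 assumed features, two endpoints) it is Φ(2.90 − 4.21), about 9%. A false discovery rate procedure should cost less power, though its threshold cannot be computed before the data exist.

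The cost is fewer features declared significant, a short protocol edit, and the work of specifying and running the validation. Section 43 commits all analysis to one named SAS release, so it should allow other software if the validation needs it. No additional patients, samples or procedures are required.
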